## Methods and analysis

### Polygenic risk score analyses

PRS can be developed using GWAS summary statistics on the associations of many SNPs across the genome with cancer. In this way millions of SNPs can be combined to develop an individual’s PRS for a cancer. A PRS is the sum of the number of copies of risk alleles individuals have for SNPs across the genome, weighted by the effect size of these SNPs in relation to the disease of interest, in this case, cancer [19]. While the initiation of cancer and the factors that contribute to the onset and progression of cancer are still not fully understood [20]; by calculating a PRS using data from all SNPs across the genome, SNPs involved in initiation, promotion and progression of cancer will be captured by this score, reflecting the complex process of cancer development [18].

In this study, PRS will be calculated for UKB participants (Application ID: 15825/81499) with proteomic measurements (N = 49,542), individuals with sex-mismatch (derived by comparing genetic sex and reported sex) or individuals with sex-chromosome aneuploidy will be excluded from the analysis (N = 814) as well as highly related individuals related to a 3^rd^ degree to >200 individuals (N = 2) [21]. For colorectal cancer, we will use effect weights derived from GWAS summary statistics of the: i) Genetics and Epidemiology of Colorectal Cancer Consortium (GECCO) (GWAS Catalog Accession: GCST90255675) for Europeans; and ii) the Asia Colorectal Cancer Consortium (ACCC)/Korean-National Cancer Centre CRC Study 2 (Korea-NCC2) for GWAS summary statistics for East Asians. For lung cancer, we will use effect weights derived from GWAS summary statistics from the International Lung Cancer Consortium (ILCCO) (GWAS Catalog Accession: GCST004748). Sample selection and quality control within these studies has been previously described [22,23].

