### Olink proteins

Olink protein measurements were performed as part of the Pharma Proteomic Project (UKB-PPP) on blood plasma samples using the antibody-based protein Olink Explore 3072 Proximity Extension Assay. Proteomics were generated for 54,219 participants who were considered to be highly representative of the UK Biobank population on baseline characteristics and showed enrichment for selected diseases [30]. The number of participants with colorectal and lung cancers can be seen in Table 1. Quality control, sample selection and data processing has been described previously [30]. Associations between the participants’ PRS and 2923 Olink protein measures from the UK Biobank will be tested via linear regression, adjusting for age, sex, principal components and sample storage time where this has an impact on protein level variation [31]. Protein measures will undergo inverse rank normal transformation (INT) for each protein [32]. The number of independent proteins will be calculated using the metaboprep R package [33]. False discovery rate correction will be applied to p-values, proteins with p-value less than the calculated alpha will be prioritised for further analyses.

**Table 1 pone.0312970.t001:** Cancer frequency within the UKB cohort and within the UKB-PPP study participants.

ICD10/ICD9 code	Cancer	Number of cases (UKB)	Number of cases (UKB-PPP)
C18/153	Malignant neoplasm of colon	6015 (1.2%)	630 (0.13%)
C19/1540	Malignant neoplasm of rectosigmoid junction	642 (0.13%)	67 (0.013%)
C20/1541	Malignant neoplasm of rectum	2670 (0.53%)	268 (0.053%)
C34/162	Malignant neoplasm of bronchus and lung	5305 (1.1%)	597 (0.12%)
**ICD-O-3 Code**	**Histological Subset**	**Number of cases (UKB)**	**Number of cases (UKB-PPP)**
8140, 8211, 8250–8260, 8310, 8323, 8480–8490, 8550	Lung adenocarcinoma	2390 (0.48%)	261 (0.052%)
8070-8072	Lung squamous cell carcinoma	1244 (0.25%)	151 (0.03%)
8041–8042	Lung small cell carcinoma	502 (0.1%)	64 (0.013%)

Number of cases for each cancer type derived from UK Biobank phenotypic data with percentage of cases out of overall individuals is represented in brackets. UKB overall n = 501939, UKB with protein measures (UKB-PPP) n = 52996.

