### Study design

MR will be performed in the forward and reverse direction: forward MR, where the protein is the exposure and cancer is the outcome, will be used to estimate the effect of selected proteins on the cancer of interest and reverse MR, where cancer is the exposure and protein levels are the outcomes, will be used to estimate the effect of cancer liability on circulating protein concentration [17]. Forward MR will be performed using cis-pQTLs to instrument proteins identified as being associated with the cancer PRS, the threshold for these will be p < 3.4 x 10^−11^ [40]. Cis-pQTLs will be defined as within < 1Mbp of the protein coding gene and trans-pQTLs will be defined as > 1Mbp away from the protein coding gene [41]. Reverse MR will be performed using SNPs associated with the cancer PRS at a threshold of p < 5 x 10^−8^ excluding cis-pQTLs for the protein. If association is found in the forward direction this may suggest that the protein is causal for the cancer but if association is found in the reverse direction this may suggest that genetic liability to cancer is causing the protein level change [17]; to elucidate this causality, different MR estimation methods will be employed, the application and conditions of these are described below.

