**Fig 3 pone.0312970.g003:**
[figure not shown]
Flowchart of methodology and data selection. UK Biobank data will be filtered based on exclusion criteria and availability of protein data, this will filter into proteins identified. Cis-pQTLs for the proteins will be identified which will either by used as instruments for forward MR or excluded from reverse MR. Various MR analyses will be performed based on number of SNPs available and sensitivity analyses will be used to filter proteins to perform colocalization.

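### The only cis-pQTL cut-off given, p < 3.4e-11, appears also to decide which SNPs leave reverse MR, so cis SNPs with clear protein effects can stay in as cancer instruments

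*Protocol article*

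**What the plan says.** All in the Protocol article:

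- Study design, forward MR: proteins are instrumented by cis-pQTLs, and "the threshold for these will be p < 3.4 x 10" to the power −11. No other p-value for cis-pQTLs appears.
- Study design, next sentence: "Cis-pQTLs will be defined as within < 1Mbp of the protein coding gene". This sentence mentions distance only.
- Study design, reverse MR: "Reverse MR will be performed using SNPs associated with the cancer PRS at a threshold of p < 5 x 10" to the power −8, "excluding cis-pQTLs for the protein". No separate threshold or window is given for this exclusion.
- Fig 3 legend: "Cis-pQTLs for the proteins will be identified which will either by used as instruments for forward MR or excluded from reverse MR". This describes one identified set with two uses.
- Instrument & method selection: Wald ratio for one SNP, fixed-effects IVW for two or three, random-effects IVW for four or more. Cochran's Q, MR-PRESSO, weighted median and weighted mode are also planned, and the pleiotropy assessment is repeated in both directions. Clustering methods and colocalization follow in later paragraphs.

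**The concern.** A strict cut-off has opposite effects in its two uses. For choosing forward instruments it is cautious, because only SNPs with a very firm effect on the protein get in. For deciding what to leave out of reverse MR it is lax, because anything short of very firm stays in.

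The exclusion exists because a SNP beside the protein's own gene may act on the protein directly. Used as an instrument for cancer liability, such a SNP breaks the exclusion-restriction assumption (IV3 in the Assumptions section). Its association with the protein can then be read as an effect of cancer liability on the protein, which is the category the study sets out to find.

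The error also leans one way. Suppose a protein's best cis signal lies between 5e-8 and 3.4e-11. It has no forward instrument, so forward MR cannot support the rival explanation that the protein causes cancer. The same SNP, if it is also a cancer SNP, remains in reverse MR.

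**Working it through.** The plan gives no derivation for 3.4e-11, so there is no figure of its own to reproduce. The check asks what the cut-off lets through and what that does to the planned estimators.

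**Inputs from the protocol.** Cut-off 3.4e-11 and conventional 5e-8 (Study design); participants "with proteomic measurements (N = 49,542"), taken here as the sample for the protein associations (Polygenic risk score analyses); F > 10 as the mark of an adequate instrument, and the estimator rules (Instrument & method selection).

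**Assumptions not in the protocol.** The number of reverse-MR instruments; the share s of total instrument strength carried by the cis SNP; one retained cis SNP; all other SNPs null for the protein; no true effect of cancer liability.

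**Step 1: what stays in.** z comes from the two-sided p, F = z², R² = F/(N − 2 + F).

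| p for protein | z | F | R² at N = 49,542 |
|---|---|---|---|
| 3.4e-11 | 6.63 | 43.9 | 0.089% |
| 5e-8 | 5.45 | 29.7 | 0.060% |

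A cis SNP with F anywhere from 10 to 43.9 passes the plan's own strength rule as an instrument for the protein, yet is not removed from reverse MR. The chance that a SNP is retained is Φ(6.63 − true z): 95% at true z = 5, 88% at 5.45, 74% at 6 and 55% at 6.5. z and F do not depend on N. With the 52,996 participants of Table 1, the R² at the cut-off is 0.083%.

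**Step 2: one to three instruments.** With one SNP the Wald ratio has the SNP's own z of 5.45, so it is always significant. With K SNPs under fixed-effects IVW, the statistic is distributed N(√s·z, 1 − s). At equal weights (s = 1/K) and z = 5.45:

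- K = 2: mean 3.85, SD 0.71, so P(> 1.96) is above 99%.
- K = 3: mean 3.15, SD 0.82, so P(> 1.96) = 93%.

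If the cis SNP's observed z is instead allowed to vary (true z = 5.5, retained only when below 6.63), the rates are 97% and 87%.

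**Step 3: four or more instruments.** Random-effects IVW divides the statistic by √max(1, Q/(K − 1)), so the outlier inflates its own standard error.

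- *K = 10, equal weights (s = 0.10).* Numerator √0.10 × 5.45 = 1.72. Expected Q = 29.70 + 9 − (2.97 + 0.90) = 34.83; Q/9 = 3.87, with root 1.97. The statistic is about 1.72/1.97 = 0.88, well short of 1.96.
- *K = 50, s = 0.20.* Numerator √0.20 × 5.45 = 2.44. Expected Q = 29.70 + 49 − (5.94 + 0.80) = 71.96; Q/49 = 1.47, with root 1.21. The statistic is about 2.44/1.21 = 2.01, so roughly half of cases exceed 1.96.

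Simulation of the same model at z = 5.45 gives:

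| Setting | False significance at 5% | Cochran's Q flags (5%) |
|---|---|---|
| Equal weights, 5, 10, 20 SNPs | 2.4%, 3.3%, 4.4% | at least 99.9% |
| 50 SNPs, s = 5% | 12% | 84% |
| 50 SNPs, s = 10% | 25% | 79% |
| 50 SNPs, s = 20% | 53% | 69% |

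In the last three rows the cis SNP's effect on cancer, scaled by the standard error of its protein association, is √(49s/(1 − s)) times that of each other SNP: 1.6, 2.3 and 3.5 times.

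**Step 4: after the change.** With a purely positional exclusion no cis SNP remains, and simulated rejection returns to about 4–5%.

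**The case against.** **The plan may mean distance only.** The defining sentence uses distance alone, the p-value stands in the sentence on forward instruments, and no sentence says that 3.4e-11 governs the exclusion. A reader might infer that the plan states this outright. It does not. The reading rests on the single cut-off being attached to cis-pQTLs, on the word pQTL (a SNP associated with the protein), and on the Fig 3 legend's single identified set. If distance only was meant, the problem disappears once that is written.

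**An article may leave filters to a fuller plan.** That is fair for details. Here, however, the article does fix a cut-off and links the two uses, and the point concerns what it fixes.

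**The size is easily overstated.** A fixed-effect calculation for shares of 5%, 10% and 20% gives 22%, 40% and 70% false significance at z = 5.45, and a reader might take such rates as general. The plan prescribes random-effects IVW from four SNPs upward, and with equal weights the inflation vanishes. This objection stands: the harm needs either very few instruments or a cis SNP that is unusually strong for cancer. The plan does not give the number of reverse instruments and speaks of larger numbers for reverse MR.

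**The planned checks would catch it.** Often they would. Q flags nearly every run with up to 20 equal-weight SNPs, and MR-PRESSO, median and mode estimates, clustering and colocalization all bear on a single outlying SNP. But Q loses power where the bias is worst: with two or three SNPs and a cis SNP four times as strong, it flags only 24–33% of runs. Weighted median and mode, as estimators, are planned only above 10 SNPs. By the Fig 3 legend, colocalization comes after the sensitivity analyses have filtered the proteins.

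**A further tempting inference** is that 3.4e-11 was set for the wrong panel, since 5e-8/3.4e-11 is about 1,471 and the panel has 2,923 proteins. The protocol does not say how the cut-off was derived and cites a source not at hand, so this is not supported. A cut-off of 5e-8/2,923 = 1.7e-11 would in any case be stricter and retain more cis SNPs.

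**Conclusion.** The point holds in conditional form. On the natural reading, cis SNPs with protein |z| up to 6.63 (0.089% of protein variance at N = 49,542) remain instruments for cancer in reverse MR, against the purpose of the exclusion and against IV3.

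With no true effect and one retained cis SNP at z = 5.45, false significance is about 93–100% with one to three equal-weight instruments and about 12–53% with 50 SNPs when the cis SNP carries 5–20% of instrument strength. It is about 2–5%, so not inflated, when four or more SNPs carry equal weight. These figures depend on instrument numbers and shares that the protocol does not give.

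The documents do not support the stronger claim that affected proteins will be classed as downstream of cancer. The plan says only that a reverse association may suggest this, and it schedules further checks. Those checks reduce the risk without removing it. Only proteins with a genome-wide significant cancer SNP in their own cis window, and a protein effect short of the cut-off, are exposed.

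**What to change.** Separate the two roles in the Study design section and in the Fig 3 legend. Keep p < 3.4e-11 only for choosing forward-MR instruments. For reverse MR, state that every cancer SNP within 1 Mbp of the protein-coding gene is excluded, whatever its p-value for that protein. If this is already the intention, the same sentence settles it.

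The cost is one sentence and a positional filter. For each protein, the few cancer SNPs lying in its cis window are lost, with a small loss of reverse-MR precision. The planned pleiotropy checks stay as they are.

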### Instrument & method selection

The strength of instrument will be determined by calculating the F-statistic, a measure of potential weak instrument bias that could arise from the use of IVs as a proxy for the effect of exposure on outcome [39]. The F-statistic takes into account the genetic variance (R^2^), the sample size and how many instruments are present. An F-statistic greater than 10 indicates that the bias from weak instruments is small, where this F-stat is less than 10 this indicates a possibility of bias and will be noted [42].

Dependent on the number of SNPs available, the appropriate method of effect-estimation will be selected for MR analyses. For proteins with a single pQTL SNP the Wald ratio will be calculated as the ratio of SNP-outcome/SNP-exposure association [43]. For proteins with two or three independent SNPs, a fixed-effects inverse variance weighted (IVW) model will be used. For four or more independent SNPs, a random effects inverse variance (IVW) model, combining multiple SNP outcome/exposure Wald ratio, will be used [44]. In the event of multiple independent SNPs, pleiotropy will be considered by calculating Cochran’s Q statistic, a method for assessing global and individual pleiotropy across instruments [45]. Weighted mode and weighted median methods will also be used when > 10 SNPs are available [46,47].

The MR-PRESSO, weighted mode and weighted median methods will be used to assess IVs for horizontal pleiotropy, violation of IV3 where the IV acts on the outcome not via the exposure, by comparing estimates with and without suspected pleiotropic variants, this will be repeated for both forward and reverse MR [48]. In addition being robust to pleiotropy methods such as MR robust adjusted profile score (RAPS) also accounts for other potential sources of bias such as weak instruments and measurement error in the exposure [49]. MR-CAUSE (Causal Analysis Using Summary Effect estimates) is another method that can be used when IV3 is violated due to pleiotropic effects of correlated pleiotropy, where the pleiotropic factor is a confounder of the exposure-outcome association versus when the IV has effects on pleiotropic factor independently of the effect of the IV on the exposure this is uncorrelated pleiotropy [50].

When performing reverse MR using a larger numbers of SNPs, clustered heterogeneity can occur when different genetic variants are causally associated via distinct pathways. To assess this, clustering based methods can be used to divide groups based on these estimates of causality [51]. MR-Clust will be used to investigate clustered heterogeneity across IVs and identify potential distinct pathways that make up the effect estimate; clustering works by separating the variants into clusters with additional null and junk clusters, representing no causal effect or those that do not fit within the distinct clusters [51,52]. Another clustering method that will be used is the Noise-Augmented von Mises-Fisher Mixture model (NAvMix), this method allows for variants to belong to multiple clusters based on their probability of membership to that cluster [53,54]. The contamination mixture model method can also be used to cluster into distinct groups based on the IVs causal effect estimate even when invalid IVs are present [55]. PheWAS-based clustering will also be used to cluster SNP associations based on different pathways and thus help identify other causal pathways of the PRS – protein associations found [56]. The methods of MR described make different assumptions and aim to address different violation of the IV assumptions, testing of these different methods has illustrated the variation in accuracy and the need for appropriate method selection based on the datasets used [57].

### Data harmonisation

Harmonisation across the GWAS summary statistics datasets will be performed using the TwoSampleMR R package to ensure that the effect on exposure and outcome are in the same direction, using effect allele frequency (EAF) to infer the strand, palindromic SNPs are kept where they are inferable from EAF. [58].

### Colocalization

Associations may be due to genomic confounding, where genetic variants in linkage disequilibrium (LD) at the same locus act on the cancer and protein via separate pathways, a form of horizontal pleiotropy bias. Colocalization analyses will be used to assess if genetic associations with cancer and proteins are due to shared causal variants at the same locus through genomic confounding [59,60].

A full overview of the sample selection and filtering of available data is shown in Fig 3, including the number of participants after filtering and results to be taken forward.

**Fig 3 pone.0312970.g003:**
[figure not shown]
Flowchart of methodology and data selection. UK Biobank data will be filtered based on exclusion criteria and availability of protein data, this will filter into proteins identified. Cis-pQTLs for the proteins will be identified which will either by used as instruments for forward MR or excluded from reverse MR. Various MR analyses will be performed based on number of SNPs available and sensitivity analyses will be used to filter proteins to perform colocalization.

### Ethics

The colorectal cancer GWAS conducted by Fernandez-Rozadilla et al. (2022) was approved by the South Central Ethics Committee (UK) under the reference number 17/SC/0079 [22].

All studies used in the lung cancer GWAS conducted by McKay et al. (2017) obtained local ethics committee approval and all participants gave informed consent [23].

Application for colorectal cancer site specific GWAS summary statistics from GECCO has been approved.

Application for summary statistics from the Asian Colorectal Cancer Consortium (ACCC) and the Korean-National Cancer Center CRC Study 2 (Korea-NCC2) will be submitted.

UK Biobank was approved by the North West Multi-centre Research Ethics Committee (MREC) as a Research Tissue Bank (RTB) approval renewed in 2021, all participants in the study have given informed consent [61]. Genotype, phenotype and Olink protein measure data access has been obtained under Application ID: 15825/81499.

### Further analyses

#### “Time-to” and “Time-from” diagnosis.

In observational analyses, we will evaluate the magnitude of the relationship between proteins, taken either pre or post-diagnosis, and cancer risk. This will involve an analysis of prevalent and incident cancer cases in UKB (Table 2) and a time variable derived from date of cancer diagnosis and time of blood collection [62,63]. To adjust for any variation in protein concentration as a result of sample storage and protein degradation over time [31], the relationship between storage time and protein level for all protein measures available will be assessed. Proteins are more likely to be causally downstream of cancer onset if the association with cancer is sensitive to time between protein measure and cancer diagnosis, a potential route for differentiating between normal baseline levels and levels that suggest the presence of cancer. If protein levels are detectable prior to patient reported symptoms proteins may be more suited for screening and early detection.

**Table 2 pone.0312970.t002:** Prevalent and incident cases of cancer from UKB cohort and within the UKB-PPP study participants.

ICD10/ICD9 Code	Cancer	UKB Overall		UKB-PPP	
		Prevalent Cases	Incident Cases	Prevalent Cases	Incident Cases
C18/153	Malignant neoplasm of colon	1029	4986	97	533
C19/1540	Malignant neoplasm of rectosigmoid junction	186	456	22	45
C20/1541	Malignant neoplasm of rectum	574	2096	60	208
C34/162	Malignant neoplasm of bronchus and lung	245	5060	31	566
**ICD-O-3 Code**	**Histological Subset**	**Prevalent Cases**	**Incident Cases**	**Prevalent Cases**	**Incident Cases**
8140, 8211, 8250–8260, 8310, 8323, 8480–8490, 8550	Lung adenocarcinoma	77	2313	8	253
8070-8072	Lung squamous cell carcinoma	74	1170	14	137
8041–8042	Lung small cell carcinoma	23	479	3	61

Number of incident and prevalent cases for each cancer type derived from UK biobank phenotypic data.

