**Methods and analysis:**

PRS will be calculated using the PRS continuous shrinkage approach (PRS-CS and PRS-CSx) for colorectal and lung cancer risk. This methodology utilises effect sizes from summary statistics from genome-wide association studies (GWAS) available for the cancers of interest to generate weights via the continuous shrinkage approach which incorporates the strengths of the GWAS associations into the shrinkage applied. This methodology both improves upon previous PRS methods in accuracy as well as improving cross-ancestry application in the PRS-CSx approach. GWAS summary statistics will be from the Genetics and Epidemiology of Colorectal Cancer Consortium (GECCO) and the International Lung Cancer Consortium (ILCCO). The association between the polygenic risk scores and 2923 proteins measured by the Olink platform in UK Biobank (UKB) participants with protein measures available will be assessed using linear regression under the assumption of linearity in the proteomic data. The proteins identified could represent several different scenarios of association such as forward causation (protein causes cancer), reverse causation (cancer genetic liability causes protein level change), or horizontal pleiotropy bias (no causal relationship exists between the protein and cancer). Forward and reverse Mendelian randomization sensitivity analyses, as well as colocalization analysis, will be performed in efforts to distinguish between these three scenarios. Protein changes identified as causally downstream of genetic liability to cancer could reflect processes occurring prior to, or after, cancer onset. Due to individuals in the UKB having proteins measures at only one timepoint, and because UKB contains a mix of incident and prevalent cases, some protein measures will have been made prior to a cancer diagnosis while others will have been made after a cancer diagnosis. We will explore the strength of association in relation to the time between protein measurement and prevalent or incident cancer diagnosis.

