### Aims and objective

Cancer early detection remains a challenge, with a lack of specific biomarkers for lung and colorectal cancer. This research aims to identify protein level changes that are causally downstream of genetic liability to lung cancer and colorectal cancer for use as potential biomarkers for these cancers. To achieve this, we will use a combination of PRS, observational analyses, bidirectional Mendelian Randomization and colocalization approaches.

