### Strengths and limitations of this study

Strengths of the study:A strength of using PRS in the discovery step of identifying proteins to carry through into MR, is that lifetime genetic liability to cancer is captured with the use of a continuous measure of genetic risk. In contrast, using cancer registry data only captures those who already have a diagnosis and not those who may go on to be diagnosed imminently.This study will use a novel approach to construct PRS using weights generated from SNPs across the genome, we expect this to be more powerful for discovery in comparison with a PRS constructed using only genome-wide significant SNPs.Limitations of the studyLack of protein data for diverse population groups within available datasets; therefore, results may not be generalisable to ancestries outside of the European population for whom sufficient protein data was available for this study.UKB participants reflect a subset of the population that volunteered for the study, participants are from a higher socioeconomic position than average which could introduce collider bias.Prevalent cancer cases will reflect a specific subset of the general population with cancer, individuals who have survived cancer and were able to volunteer for the study; potentially introducing survivorship bias.It cannot be ruled out that proteins may reflect effects of processes beyond cancer liability to protein pathways.Lack of staging information for cancer cases within the UKB limiting our ability to distinguish early versus more advanced cancers.The proteomic technology currently used measures protein binding as opposed to protein levelsSubgroup analyses are more prone to false positive results which will require replication analysis to ensure these reflect actual associations.Power calculations have not been performed to assess the power of the subgroup analyses.

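### The time-sensitivity inference is not limited to pre-diagnosis samples, so a treatment-affected protein could be misread as one that marks cancer

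*Protocol article*

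**What the plan says.** The section on time to and time from diagnosis, under Further analyses, states the purpose: "we will evaluate the magnitude of the relationship between proteins, taken either pre or post-diagnosis, and cancer risk". On the cases and the time variable it says: "This will involve an analysis of prevalent and incident cancer cases in UKB (Table 2) and a time variable derived from date of cancer diagnosis". The other end of that interval is when the blood was drawn. The abstract gives the same scope: "We will explore the strength of association in relation to the time between protein measurement and prevalent or incident cancer diagnosis".

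The section draws one inference from the time pattern. A protein is "more likely to be causally downstream of cancer onset if the association with cancer is sensitive to time between protein measure and cancer diagnosis". Nothing confines this to samples drawn before diagnosis. The only adjustment discussed there is for storage: "the relationship between storage time and protein level for all protein measures available will be assessed".

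The abstract also notes a constraint of the data: "Due to individuals in the UKB having proteins measures at only one timepoint". The limitations describe prevalent cases as "individuals who have survived cancer and were able to volunteer for the study; potentially introducing survivorship bias". Cancer treatment is not mentioned anywhere in the article as an influence on protein levels. The stated aim is to find proteins "for use as potential biomarkers for these cancers".

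**The concern.** The Introduction gives the reasoning behind the inference: proteins downstream of cancer should vary as the disease progresses. Before diagnosis, time to diagnosis is a plausible index of progression. After diagnosis it is a mixture. Time since diagnosis runs alongside surgery, systemic treatment, recovery and the loss of patients who die early. A gradient in post-diagnosis samples therefore does not identify the mechanism that the inference assumes.

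The error can go either way. A protein changed only by treatment can look time-sensitive and gain support as downstream of cancer. A genuine tumour product that clears quickly after resection can look flat if post-diagnosis samples are read alone. Repeated samples from one person could help to separate these cases, but each participant has only one.

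At stake is whether a candidate protein signals that cancer is present. In a literal sense a treatment effect is also downstream of onset, but it does not signal that.

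**Working it through.** **1. Case counts.** Inputs are the UKB-PPP columns of Table 2 (prevalent, incident) and the UKB-PPP totals of Table 1. Prevalent plus incident should equal the Table 1 total.

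| Site | Prevalent | Incident | Sum | Table 1 | Prevalent share |
|---|---|---|---|---|---|
| Colon | 97 | 533 | 630 | 630 | 15.4% |
| Rectosigmoid junction | 22 | 45 | 67 | 67 | 32.8% |
| Rectum | 60 | 208 | 268 | 268 | 22.4% |
| Lung | 31 | 566 | 597 | 597 | 5.2% |

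The three lung histology rows also agree (8 + 253 = 261; 14 + 137 = 151; 3 + 61 = 64). The plan's own figures are reproduced.

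Colorectal sum: prevalent 97 + 22 + 60 = 179; incident 533 + 45 + 208 = 786; total 965. Prevalent share 179/965 = 18.5%. This assumes that no participant appears under two colorectal codes, which the article does not state.

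**2. Could a treatment-only protein be flagged?** The documents give no effect sizes or time distributions, so this step is illustrative. Assumptions:
- protein SD of 1 and no change at all before diagnosis;
- pre-diagnosis times uniform over 0 to 12 years, post-diagnosis times uniform over 0 to 10 years;
- a treatment effect of 0.5 or 1.0 SD decaying exponentially with a 3-year constant, or a lasting 0.5 SD shift;
- linear regression of protein on time among cases, two-sided 0.05, 2,000 runs per scenario.

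Share of runs in which the protein is flagged as time-sensitive (0.5 SD decaying / 1.0 SD decaying / 0.5 SD lasting):

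| Time variable | Colorectal (179 post, 786 pre) | Lung (31 post, 566 pre) |
|---|---|---|
| Signed time, pre and post pooled | 17% / 53% / 99.7% | 6% / 11% / 34% |
| Absolute time, pre and post pooled | 13% / 34% / 11% | 5% / 6% / 4% |
| Post-diagnosis only | 33% / 89% / 5% | 10% / 24% / 5% |
| Pre-diagnosis only | about 5% throughout | 4% to 5% |

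With no treatment effect, every version gives 5% to 6%. Only the pre-diagnosis version stays at the nominal rate in all scenarios. Modelling the two sides separately is not enough by itself, because the post-diagnosis slope still picks up a decaying treatment effect.

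**3. What incident cases alone can detect.** For 80% power at two-sided alpha 0.05, with a large comparison group, the detectable case-control mean shift is (1.96 + 0.84)/√n = 2.80/√n SD.
- Colorectal: 2.80/√786 = 0.10 SD.
- Lung: 2.80/√566 = 0.12 SD.

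These are mean shifts and not time gradients. If times to diagnosis were uniform over a window of width W (an assumption), the SD of time is W/√12. The detectable change across the whole window is then √12 × 2.80/√n.
- Colorectal: 3.464 × 0.0999 = 0.35 SD.
- Lung: 3.464 × 0.1177 = 0.41 SD.

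Both are before any correction for multiplicity.

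**The case against.** The strongest reply is that this is exploratory supporting evidence. The inference is worded as a likelihood and presented as one possible route. No threshold, filter or label rests on it. Causal direction is addressed mainly by bidirectional Mendelian randomization and colocalization. Suitability for screening has its own sentence with its own condition, that levels be detectable before symptoms. The section heading and the split in Table 2 suggest that the two directions may be examined separately, and no pooled model is stated. Besides survivorship, the limitations include a general caveat that proteins may reflect other processes. Most records are pre-diagnosis.

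Much of this stands. A reader might infer that the plan will label treatment effects as downstream proteins, or that this analysis decides which proteins suit screening. The text supports neither reading. A reader might also infer that post-diagnosis samples are worthless. They are not: a protein raised before diagnosis that falls back afterwards is real supporting evidence of tumour origin. Nor does the article commit to a time-from-diagnosis analysis by lung histology. With 3 prevalent small-cell cases a slope could be computed but would be uninformative.

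What the reply does not remove is the scope of the inference. It is stated for samples on both sides of diagnosis. Neither limitation restricts it or names treatment. Selecting proteins by polygenic score first would not remove the problem, because an upstream or pleiotropic protein that treatment also moves would still look time-sensitive. The article does not say that the time analysis is confined to selected proteins.

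**Conclusion.** The point holds as a risk of misreading. As written, a post-diagnosis gradient caused by treatment or selective survival can count as support for a protein being driven by cancer. The exposure is material for colorectal cancer (18.5% of case records, and 32.8% for the rectosigmoid junction). It is small for lung (5.2%) unless the post-diagnosis results are read on their own.

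The case shares come directly from Table 2, with the no-double-coding assumption for the colorectal sum. The flag rates depend entirely on the assumed effect sizes and timings. They show the direction of the problem and how it differs by model, and they do not predict how many proteins would be affected.

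**What to change.** - Base the downstream inference on incident cases only: time from blood draw to diagnosis, compared with participants free of that cancer.
- Model prevalent cases separately. Report time-from-diagnosis results, including any contrast with pre-diagnosis levels, as descriptive or supporting evidence that is not sufficient for a downstream label.
- Add treatment to the limitations, beside survivorship.

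The cost is wording and model specification, with no new data. The inference loses 179 colorectal and 31 lung case records. It keeps 786 of 965 (81.5%) and 566 of 597 (94.8%). Any statement about the precision of the restricted analysis should use the time-gradient figures and not the smaller mean-shift ones.
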